## **7.0 SCREENING OF SUBJECTS**

### **7.1 Inclusion Criteria**

A subject must meet all the following inclusion criteria in order to be enrolled in this study:

1. Age  $\geq 18$  years old.
2. Histologically or cytologically confirmed NSCLC, which is confirmed by imaging as advanced NSCLC with brain metastases (including stage IV patients who are newly diagnosed or have relapsed after previous surgical treatment; according to the AJCC 8th edition lung cancer staging criteria).
3. Confirmed as EGFR-sensitive mutations in tumor tissue samples or blood samples by local laboratory (including exon 19 deletion or L858R, either existing alone or co-existing with other EGFR site mutations). If tumor tissues are available, the tumor tissue is recommended for testing; if tumor tissues are not available or the patient cannot undergo tissue biopsy, blood samples may be tested.
4. Have not received any systemic treatment after the diagnosis of NSCLC with metastases to brain parenchyma. For patients who have received local treatment, the lesion within the scope of the local treatment cannot be used as the target lesion unless the lesion has progressed.
5. Patients with at least 1 extracranial target lesion (measurable lesions that have not undergone local treatment such as irradiation or have shown definitive after local treatment, with a baseline longest diameter  $\geq 10$  mm (or  $\geq 15$  mm for lymph nodes)) and at least 1 intracranial lesion (with a baseline longest diameter  $\geq 5$  mm).
6. The brain condition is stable or that were controlled with anticonvulsants or dexamethasone at a maximum dose of 5 mg daily before the study treatment.
7. An Eastern Cooperative Oncology Group (ECOG) performance status score of 0 or 1, with no worsening over at least 2 weeks before study treatment, and a minimum expected survival of 3 months.
8. Female patients of childbearing potential are willing to take appropriate contraceptive measures and should not breastfeed from signing the informed consent to 6 months after the last dose of study treatment; male patients are willing to take barrier contraception (i.e., condoms) from signing the informed consent to 6 months after the last dose study treatment.
9. Female patients of childbearing potential must have a negative serum or urine HCG test within 7 days before enrollment in the study, and they must be non-lactating.
10. The subject voluntarily participates and signs the informed consent form in writing.

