### **7.2 Exclusion Criteria**

A subject will not be eligible for inclusion in this study if any of the following criteria apply:

1. Treatment with any of the following:
  - a. Previously received treatment with tyrosine kinase inhibitors against EGFR (such as erlotinib, gefitinib, icotinib, afatinib, osimertinib, and aumolertinib);
  - b. The patient has undergone major surgery (such as craniotomy, thoracotomy, or laparotomy) within 4 weeks before the first dose of the investigational medicinal product, or undergone minor traumatic surgery (biopsy, bronchoscopy, and thoracic drainage) within 7 days before the first dose of the investigational medicinal product. Major surgeries are defined as Grade 3 and Grade 4 surgeries specified in the "Administrative Measures for Clinical Application of Medical Technology" implemented from Nov. 1, 2018 in Appendix H;
  - c. Patients who have received local radiotherapy within 2 weeks before the first dose of the investigational medicinal product; patients who have received more than 30% of bone marrow irradiation (see Appendix I for the calculated area of bone marrow) or extensive radiotherapy within 4 weeks before the first dose of the investigational medicinal product; patients who have received whole brain radiotherapy for this disease before enrollment;
  - d. Recurrence within 6 months after adjuvant or neoadjuvant treatment for early lung cancer; if there is both neoadjuvant therapy and adjuvant therapy, the adjuvant treatment time will be used for calculation;
  - e. Within 14 days before the first dose of the investigational medicinal product, traditional Chinese medicines and their preparations with anti-tumor effect or adjuvant anti-tumor effect have been used (see Appendix E for the list of drugs);
  - f. Presence of pleural/abdominal effusion requiring clinical intervention (patients who do not require drainage of the effusion or are stable for more than 2 weeks after drainage of the effusion are eligible); presence of pericardial effusion (patients with small amount of pericardial effusion who are stable for 2 weeks or more are eligible). If anti-tumor drugs are used locally (e.g., via intrapleural infusion) during drainage, patients are only eligible with a washout of at least 5 half-lives or 21 days (whichever is shorter) prior to the first dose of study treatment;

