### 9.1.3.4 Follow-up of patients after any disease progression

At the time of disease progression assessment, 3 sets of assessments will be performed in this study: systematic assessment, intracranial assessment, and extracranial assessment. During the overall assessment, extracranial and intracranial target lesions (no more than 5 target lesions in the whole body and at least one target lesion in the skull) will be selected according to RECIST 1.1, and then the selected intracranial and extracranial lesions will be subjected to separate intracranial and extracranial response evaluation according to the RECIST 1.1. There is no need to select additional intracranial or extracranial target lesions. See Table 3 for systemic, intracranial, and extracranial disease progression, subsequent anti-tumor therapies, and recommendations for data collection.

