response (PR), stable disease (SD), and progressive disease (PD). The analysis of the primary endpoint of this study will be based on the tumor response assessment made by the investigator as per RECIST 1.1, and the investigator will also manage the subjects based solely on the assessment results, unless medically contraindicated or faced with force majeure factors (such as update of the examination instrument by the study site). Baseline CT or MRI assessments of the chest, abdomen, and brain tissues must be performed within 28 days before the start of study treatment (not subject to the time of signing the ICF), and should be performed as close as possible to the start of study treatment. The investigator should perform additional imaging examinations based on subjects' signs and/or symptoms. The subsequent follow-up assessments should be performed using the method (CT/MRI) that is the same as that for baseline assessment. All enrolled subjects must have brain metastases as target lesions, and baseline imaging assessment of the brain must be performed, with MRI (enhanced) as the preferred examination method. Bone scans should be performed if there are indications for bone metastases (results within 3 months are acceptable), and positive sites found by bone scans should be confirmed by CT/MRI/X-ray. Only confirmed lesions can be recorded as non-target lesions. Subsequently, the bone metastases should be followed up by the same examination method as at baseline. During the study, bone scans may be added as needed. During the treatment period, tumor response assessment will be performed once every 8 weeks ( $\pm 1$  week) until progressive disease assessed by investigator per RECIST 1.1 (see Section 12.1.3 or 9.1.3.4). Tumor assessments should be performed according to the study plan whenever possible. If subjects are assessed at a time point beyond the scheduled time window ( $\pm 1$  week) and no progressive disease occurs, they should undergo subsequent assessments at the pre-specified time points whenever possible while continuing study treatment. If tumors are suspected at any other sites, the corresponding imaging examinations should be performed at the relevant sites. To achieve progression on the basis of the non-target lesion(s), there must be an overall level of substantial worsening in non-target lesion(s) such that, even in the presence of SD or PR in the target lesion(s), the overall tumor burden has increased sufficiently to merit discontinuation of treatment. A modest increase in the size of one or more non-target lesions is generally not sufficient to qualify for progression; therefore, it is uncommon to define overall tumor progression only with changes in non-target lesions in the face of SD or PR of target lesions. At each visit, objective tumor response will be assessed as per RECIST 1.1, and classified into CR, PR, SD, and PD. For the assessment of target lesion progression, the smallest lesion size in the entire course of treatment should be taken as reference, and an increase meeting the criteria will qualify for PD. If no progressive disease occurs, tumor response (CR and PR) and stable disease (SD) should be evaluated taking baseline lesion(s) as reference.

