#### 2.2 Non-measurable lesions

a. All other lesions, including small lesions (pathological lymph nodes with the longest diameter of  $< 10$  mm or the short axis of  $\geq 10$  mm to  $< 15$  mm at baseline; nodules with the short axis of  $< 10$  mm are considered non-pathological and should not be recorded as non-target lesions [NTLs]).

b. Truly non-measurable lesions include the following: bone lesions, submeningeal disorders, ascites, pleural/pericardial effusion, inflammatory breast diseases, lymphangitis of the skin or lung, and abdominal masses/abdominal organomegaly identified by physical examination, which cannot be measured by CT or MRI.

c. Previously irradiated lesions as local post-radiation changes that may affect the size of the lesion. Therefore, previously irradiated lesions will not be considered measurable and should be selected as NTLs at baseline and followed up as part of NTL assessment.

d. Skin lesions in clinical examination.

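### Inclusion criterion 5 omits the brain target-lesion requirement set in 10.2.1 and 9.1.3.4, so a patient whose only brain lesion was locally treated without progressing can pass eligibility

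*Protocol*

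**What the plan says.** Criterion 5 in Protocol 7.1, repeated in the synopsis, treats the two lesions differently. The extracranial lesion must be a target lesion, and its bracket limits it to "measurable lesions that have not undergone local treatment such as irradiation or have shown definitive after local treatment" (a word, presumably progression, is missing after the adjective), with its own size limits. The intracranial part reads "and at least 1 intracranial lesion (with a baseline longest diameter" of at least 5 mm). It has a size condition and nothing else.

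Criterion 4, just above it, applies to any locally treated lesion, in the brain or elsewhere: "the lesion within the scope of the local treatment cannot be used as the target lesion unless the lesion has progressed".

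Two later sections require a brain target lesion. Section 10.2.1 says "All enrolled subjects must have brain metastases as target lesions, and baseline imaging assessment of the brain must be performed". Section 9.1.3.4 sets the selection rule as "no more than 5 target lesions in the whole body and at least one target lesion in the skull".

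On prior local treatment, exclusion 1c in 7.2 rules out whole-brain radiotherapy and "Patients who have received local radiotherapy within 2 weeks before the first dose of the investigational medicinal product". The synopsis version of 1c adds a parenthesis about palliative bone radiotherapy for non-target lesions, which leaves it unclear whether focal brain radiotherapy falls under the 2-week rule there. Exclusion 1b rules out craniotomy within 4 weeks.

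**The concern.** The trial is about control of brain metastases, so the brain lesion that qualifies a patient should be one on which the drug's effect can be read. The protocol intends this, since it demands a brain target lesion and says a treated, non-progressed lesion cannot serve as one. But the demand sits in the imaging and progression sections and not in the criteria that decide who enters.

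At stake is the reading of the intracranial secondary endpoints. If the only brain lesion was irradiated before entry and stays quiet, continued control may come from the radiotherapy, the drug or both. A single-arm trial has no control group in which the same carry-over would appear.

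**Working it through.** The point rests on the text and no stated figure is in dispute, so the check sets the provisions side by side.

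1. **What decides entry.** Section 6.1 (screening period) allows enrolment of subjects who meet every inclusion criterion and no exclusion criterion. Section 7.5 defines a wrongly enrolled subject as one who does not meet the eligibility criteria. Neither refers to 10.2.1 or 9.1.3.4.

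2. **Four patients run through the rules.**
   - *Only brain lesion at least 5 mm, focally irradiated more than 2 weeks before first dose, not progressed.* Nothing in 7.1 or 7.2 on brain lesions or local treatment keeps this patient out. Criterion 4 bars the lesion as a target, so 10.2.1 and 9.1.3.4 cannot be met. Section 7.5 is not triggered, because the eligibility criteria are met.
   - *Only brain lesion irradiated and then progressed.* Criterion 4 permits it as a target. Appendix D 2.2c does not: "previously irradiated lesions will not be considered measurable and should be selected as NTLs at baseline", with no exception for progression.
   - *Only brain lesion untreated, 5 mm or more but under 10 mm.* It satisfies criterion 5. Appendix D 2.1 sets measurability at 10 mm and 2.4 limits targets to measurable lesions, so it cannot be a target there.
   - *Whole-brain radiotherapy.* Excluded outright.

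3. **Where the first patient is counted.** Section 12.4.1 puts every dosed patient in the FAS and bases the results mainly on it. The patient therefore enters PFS, iPFS, iDCR and iORR.

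4. **What response the first patient can show.** With no intracranial target lesion at baseline, the target column of Appendix D Table 4 is NA. The rows left are: non-target CR gives CR; non-target non-CR/non-PD gives SD; non-target NE gives NE; non-target PD or a new lesion gives PD. There is no route to PR. SD counts as disease control under 12.1.5, so a treated lesion that merely persists adds to iDCR.

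5. **What the planned cEFR analysis does.** The cEFR is the part of the FAS with at least one measurable brain lesion, so its definition itself allows for FAS patients without one. Under Appendix D 2.2c, patients whose brain lesions were all irradiated fall outside it. If the 10 mm rule applies, so do patients with only smaller untreated lesions. The FAS and cEFR comparison thus mixes two reasons for being left out.

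6. **Scale.** One patient is 1/63 = 1.6% of the planned enrolment. The documents give no count or expected share of patients with earlier focal brain treatment.

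**The case against.** The strongest reply is that the protocol, read as a whole, already bars these patients: criterion 4, 10.2.1 and 9.1.3.4 together leave no room for someone whose only brain lesion was treated and has not progressed. That is right as to intent, and it makes this an inconsistency to reconcile, not a deliberate choice to admit such patients. It does not close the gap, because a site applying 7.1 and 7.2 as written would enrol the patient, and nothing in 7.5 or 12.4.1 would then remove the patient.

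A second reply is that efficacy is also analysed in the cEFR, which leaves out patients whose brain lesions were all irradiated. This stands in large part. The remaining weakness is that the cEFR may also drop patients with small untreated lesions and that the main results come from the FAS.

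A reader might also infer that iORR in the FAS falls in direct proportion to the share of such patients. That is too strong. It sets every one of them to non-response, whereas Table 4 allows a CR if the non-target lesion disappears. Only PR is lost.

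**Conclusion.** The inconsistency holds. Criterion 5 does not carry the protocol's own brain target-lesion requirement, and the criteria that decide enrolment let through a patient who cannot meet it. For each such patient in the FAS, iPFS and iDCR are confounded with the prior local treatment, and an intracranial PR cannot be recorded.

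A reader might go further and infer that the effect of radiotherapy is credited to the drug in the primary endpoint, inflating the chance of a positive result. The documents do not support that:
- The shift in the 12-month rate would be the share of such patients times their gain in 12-month PFS. Purely as illustration, shares of 10% to 20% with gains of 10 to 20 points give 0.10 x 10 = 1 point to 0.20 x 20 = 4 points, but neither input has any basis in the protocol.
- The primary endpoint is systemic PFS. Extracranial progression, new brain lesions and death all count, and focal treatment protects only the treated lesion.
- Section 5.3 gives no source or population for the 40% null, so it cannot be seen whether the reference patients had similar prior treatment.
- Turning a shift into an error rate needs a decision rule. Section 5.3 gives a two-sided 0.1 level, while 12.4.2.1 plans a 95% CI and states no rule.

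The size of the effect on the primary endpoint is therefore unknown. The point is worth correcting because it concerns the trial's defining lesion and costs little.

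**What to change.** In criterion 5, in both 7.1 and the synopsis, state that at least one intracranial lesion must qualify as a target lesion under criterion 4. This moves the requirement of 10.2.1 and 9.1.3.4 to the place where enrolment is decided.

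The same amendment has to settle three linked points, or the new wording will create fresh conflicts: the 5 mm entry size against the 10 mm measurability and target rules in Appendix D 2.1 and 2.4; criterion 4's allowance for progressed lesions against Appendix D 2.2c, which has none; and what a measurable brain lesion means in the cEFR definition. The two versions of exclusion 1c should be reconciled at the same time.

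For patients already enrolled whose brain lesions were all locally treated without progression, report how many there are, and give PFS, iPFS and iORR with and without them, alongside the planned FAS and cEFR analyses.

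The cost is a wording change in a few places and one sensitivity analysis. The downside is that a few patients become ineligible.

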  - g. Previously treated with drugs that are strong inhibitors or strong inducers of CYP3A4, or treated with CYP3A4 sensitive substrate drugs with a narrow therapeutic window, within 7 days prior to the first dose of investigational medicinal product; or requiring to continue the treatment with these drugs during the study (see Appendix E for the list of these drugs);
  - h. Receiving drugs known to prolong the QT interval or that may cause torsade de pointes, or requiring to continue the treatment with these drugs during the study (see Appendix E for the list of drugs and washout times);
  - i. Having participated in another clinical trial within 4 weeks or been still within 5 half-lives of the investigational medicinal product in another clinical trial before the first dose of this investigational medicinal product, whichever is longer (except for screening failure).
2. Histologically or cytologically confirmed mixed SCLC and mixed NSCLC, large cell neuroendocrine carcinoma and sarcomatoid carcinoma.
3. At the beginning of study treatment, those with residual toxicity from prior anti-tumor treatment greater than CTCAE Grade 1 that cannot be alleviated, with the exception of hair loss and Grade 2 neurotoxicity from prior anti-tumor treatment. History of intracranial hemorrhage not related to tumor.
4. History of other primary malignant tumors, except for the following:
  - a. Radically treated malignancies that have been inactive for  $\geq 5$  years prior to study enrollment and have a very low risk of recurrence;
  - b. Adequately treated non-melanoma skin cancer or lentigo maligna without evidence of disease recurrence;
  - c. Adequately treated carcinoma *in situ* without evidence of disease recurrence.
5. Diagnosis of meningeal metastasis through clinical symptoms or imaging or cerebrospinal fluid, or brain parenchymal metastasis combined with meningeal metastasis.
6. Patients who are allergic to MRI contrast agent gadolinium or who cannot tolerate MRI examinations (such as patients with pacemakers or metals in the body).
7. Any serious or poorly controlled systemic disease, such as poorly controlled hypertension, active bleeding diathesis, or active infection, as judged by the investigator. There is no need to check for chronic diseases.

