  - h. Serum albumin (ALB) < 28 g/L;
12. Female subjects who are pregnant and lactating or plan to become pregnant during the study period.
13. History of interstitial lung disease, drug-induced interstitial lung disease, radiation pneumonitis requiring steroid therapy, or any evidence of clinically active interstitial lung disease.
14. History of hypersensitivity to any active or inactive ingredients of aumolertinib or drugs of similar chemical structure or the same class as aumolertinib.
15. Any severe or uncontrolled ocular diseases (particularly severe dry eye syndrome, keratoconjunctivitis sicca, severe exposure keratitis, or other conditions that may increase the risk of epithelial damage) that may increase the safety risks of patients as judged by the physician; or patients who have any eye disorders that require surgical treatment or are expected to require surgical treatment during the study period.
16. Patients who may have poor compliance with the procedures and requirements of the study as judged by the investigator, such as patients who have a clear history of neurological or mental disorders (including epilepsy or dementia), or patients who are currently suffering from mental disorders.
17. Patients with any conditions that may jeopardize patient safety or interfere with study assessments as judged by the investigator.

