#### **7.7.4 Glucocorticoids**

Long-term systemic use of glucocorticoids is not recommended for supportive care purposes. Short-term use of glucocorticoids may be permitted for the treatment of non-autoimmune diseases (e.g., delayed allergic reactions caused by contact allergens) in individual subjects following discussion with the sponsor.

Glucocorticoids are permitted for emergency use, topical application, inhalation via spray, eye drops, or topical injection, and can be used by subjects requiring long-term inhalation of glucocorticoids at doses that do not induce systemic dose-response effects for treatment of asthma or chronic obstructive pulmonary disease. For patients with baseline symptoms of brain metastases, the use of dexamethasone at a maximum dose of 5 mg daily for symptom control is permitted. Use of systemic glucocorticoids ( $\leq 10$  mg/day prednisone or its equivalent) at physiologic replacement doses (e.g., adrenal replacement steroid dose) for treatment of diseases such as adrenal or pituitary insufficiency is permitted.

Prophylactic use of glucocorticoids according to the package insert is permitted to prevent allergic reactions (e.g., pretreatment prior to intravenous contrast agent administration).

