#### **14.2 Protocol Deviations**

The investigator should not deviate from the protocol unless it is necessary to eliminate an immediate hazard to study patients. Should other unforeseen circumstances arise that require deviation from protocol-specified procedures, the investigators should consult with the medical monitor (and IRB or IEC, if needed) to determine the appropriate course of action. The inclusion or exclusion criteria will not be subject to exemptions.

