### ■ Known sensitive substrates, strong inhibitors, and inducers of CYP3A4

#### CYP3A4 strong inducers

Carbamazepine, phenytoin, rifampin, St. John's wort, and dexamethasone; dexamethasone may be used for supportive treatment if needed at the investigator's discretion, but should be used for  $\leq 7$  consecutive days

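### Dexamethasone up to 5 mg daily is accepted by inclusion 6 and section 7.7.4, but exclusion 1g, section 7.7.3 and Appendix E treat it as a strong CYP3A4 inducer allowed for at most 7 consecutive days

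*Protocol*

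**What the plan says.** Two provisions of the protocol accept dexamethasone:

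- Section 7.1, inclusion 6 (repeated in the synopsis) admits patients whose brain condition is stable or was "controlled with anticonvulsants or dexamethasone at a maximum dose of 5 mg daily before the study treatment". It gives no duration, no washout and no restriction on which anticonvulsant.
- Section 7.7.4 says that, for patients with symptoms of brain metastases at baseline, "the use of dexamethasone at a maximum dose of 5 mg daily for symptom control is permitted". It sets no number of days.

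Three provisions restrict it:

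- Section 7.2, exclusion 1g (repeated in the synopsis) covers patients "Previously treated with drugs that are strong inhibitors or strong inducers of CYP3A4", among other classes. The window is "within 7 days prior to the first dose of investigational medicinal product; or requiring to continue the treatment with these drugs during the study". Appendix E is cited for the drug names.
- Section 7.7.3 prohibits potent CYP3A4 inducers from enrollment until 28 days after treatment stops.
- Appendix E lists the strong inducers as "Carbamazepine, phenytoin, rifampin, St. John's wort, and dexamethasone". It then adds that "dexamethasone may be used for supportive treatment if needed" in the investigator's judgement, for no more than 7 days in a row.

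Two further provisions decide what follows from a mismatch. Section 14.2 states: "The inclusion or exclusion criteria will not be subject to exemptions". Section 7.5 says that a subject who fails the criteria but has already started treatment should be withdrawn from the study.

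**The concern.** The trial enrols only patients with brain metastases, and both inclusion 6 and section 7.7.4 show that the authors expected some of them to be on dexamethasone. Exclusion 1g and Appendix E classify that same drug as one that excludes. A site that works from inclusion 6 and section 7.7.4 will enrol such a patient; a site that works from 1g and Appendix E will not. About 63 patients are planned across an estimated 20 sites, roughly three per site (63/20 = 3.15), so there is little chance for practice to settle by experience.

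Two things are at stake. One is who enters: the treated population would depend partly on which page a site reads. The other is follow-up for the primary endpoint: a treated patient later judged ineligible comes under section 7.5, and withdrawal from the study ends the tumor assessments on which the 12-month PFS rate depends.

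**Working it through.** The check is textual; no figure in the plan is involved. Section 6.1 requires every inclusion criterion to be met and no exclusion criterion to be met. Applying that rule with Appendix E as the drug list gives five cases.

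1. **Dexamethasone within the 5 mg cap, for more than 7 consecutive days, continuing.** Inclusion 6: met. Section 7.7.4: permitted, if for baseline brain-metastasis symptoms. Exclusion 1g: excluded, as both recent and continuing use. Section 7.7.3: prohibited, if Appendix E defines potent inducers. Appendix E exception: exceeded. This is a direct contradiction.
2. **Dexamethasone within the cap, for 7 consecutive days or fewer, in the week before first dose or continuing.** Inclusion 6: met. Appendix E exception: met so far. Exclusion 1g: excluded as written, because it contains no exception. The outcome depends on whether a reader carries the Appendix E exception back into 1g, so it is ambiguous.
3. **Carbamazepine or phenytoin, in the week before first dose or continuing.** Inclusion 6: met, since any anticonvulsant counts. Exclusion 1g: excluded, with no exception in Appendix E. The patient is ineligible, but nothing in inclusion 6 tells the site so.
4. **An anticonvulsant or steroid not classed in Appendix E under 1g.** No conflict.
5. **A listed inducer stopped more than 7 days before first dose and not needed again.** No conflict.

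The consequence for a case 1 patient who has been dosed can be traced as follows:

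- Section 14.2 closes the route of granting an exemption.
- Section 7.5 first asks the investigator to assess the patient and decide on stopping treatment, then says that the subject should be withdrawn from the study.
- Under section 7.8.1, patients who stop treatment for reasons other than progression keep their scheduled tumor assessments, unless they withdraw from the study.
- Under section 12.4.1 the patient stays in the full analysis set, which needs only one dose.
- Under section 12.1.2 a patient with no progression or death is censored at the last RECIST assessment.

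The net effect is early censoring, hence less information at 12 months.

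**The case against.** The strongest reply is that exclusions normally narrow inclusions. Inclusion 6 describes who may be considered, 1g removes some of them, and Appendix E supplies a dexamethasone exception. This settles carbamazepine and phenytoin: a reader might infer that such patients are both eligible and ineligible, but under section 6.1 any exclusion decides, so what remains is a missing cross-reference. It also shows that Appendix E does not bar dexamethasone outright, as a reader of the inducer list alone might infer.

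It does not settle longer dexamethasone use. Inclusion 6 could be read as covering only use that ended more than 7 days before first dose, but section 7.7.4 permits the drug on study for baseline symptoms, which 1g rules out for anyone who must continue. The opening of section 7.7.4 advises against long-term systemic glucocorticoids for supportive care; that is a recommendation and sets no limit. The allowances in section 7.7.3 and Appendix E for otherwise restricted drugs concern treatment of adverse events, not control of symptoms present at entry.

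Other stronger readings do not stand:

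- Exclusion 16 gives epilepsy as an example, but turns on the investigator's judgement of likely compliance. It does not exclude everyone on an anticonvulsant.
- Withdrawn patients do not lose their primary outcome. They remain in the full analysis set and contribute to the Kaplan-Meier estimate until censored.
- The protocol states no reason for the inducer ban, so enrolling such patients cannot be said to defeat its stated purpose.

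**Conclusion.** The point holds as an internal inconsistency in the eligibility and concomitant-medication rules. It is a firm contradiction for dexamethasone within the 5 mg cap for more than 7 days and continuing, an ambiguity for shorter use, and a missing cross-reference for carbamazepine and phenytoin.

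Its size cannot be given as a number, because the protocol does not state what share of patients takes these drugs at entry. A reader might set an assumed share of the 63 against the 14 places between the 49 required and the 63 enrolled. The documents do not support that comparison: the share would be a guess, patients screened out never count toward the 63, and not every enrolled user would be withdrawn.

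The effect on the primary endpoint is possible rather than certain. It requires that a patient be enrolled under inclusion 6, later be judged ineligible under 1g, and be withdrawn under section 7.5, whose own instructions are mixed. The effect on screening is more immediate, because every site that sees such a patient must choose between the provisions. The inconsistency should be corrected whatever the number affected.

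**What to change.** Reconcile inclusion 6, exclusion 1g, sections 7.7.3 and 7.7.4 and Appendix E, together with the synopsis copies of the two criteria:

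- State one dexamethasone rule, covering both dose and duration and both the period before first dose and the period on study, in the same terms in each place. If an exception is meant, write it into 1g itself.
- In inclusion 6, refer to the Appendix E list so that sites see which anticonvulsants fall under 1g.
- Correct the pointer in section 7.7.3. It sends the reader to Appendix D for the drug list, but Appendix D is the RECIST appendix and the list is in Appendix E.

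Which rule should apply is for the clinical team; the statistical need is only that all sites apply the same one. The cost is amendment wording. No new data are needed, since section 7.7 already records medications from 28 days before the start of treatment.
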